#### Secondary outcomes

Secondary outcomes with details on the statistical analyses are summarized in Table 1.

**Table 1 Tab1:** Summary of the secondary objectives with the statistical analysis and time of measurement

	**Secondary outcomes**	**Details of statistical analysis**^**a**^	**Time of measurement**
**Short-term mortality and comorbidity**	- Bronchopulmonary dysplasia (NICHD criteria) - Death	Logistic regressions will be performed, corrected for GA and centre, for BPD and death separately, and the combined outcome of BPD and death. Survival analysis will be performed for time to death. Cause-specific risk models will be computed to consider death as competing risk for severe disabilities at 18 to 24 months of age.	Postmenstrual age of 36 weeks and hospital discharge
	**Admission:** - Length of stay intensive care - Length of stay hospital	Survival analyses will be performed for time to discharge.	Hospital discharge
	**Respiration:** - Incidence of endotracheal intubations - Number of days on invasive ventilation - Number of days on respiratory support - Number of days with supplemental oxygen - Respiratory complications - Use of postnatal corticosteroids	Logistic regression analysis will be performed for the dichotomous respiratory complications and the use of corticosteroids. Linear regression analysis will be performed for the incidence of endotracheal intubations, and number of days on invasive ventilation, respiratory support, and supplemental oxygen. In both analyses will be corrected for GA and centre. A survival analysis will be performed for the time to intubation.	Hospital discharge
	**Gastro-intestinal:** - Solitary intestinal perforation - Necrotizing enterocolitis > stage 2 (Bell’s criteria) - Feeding problems (days with parental feeding after inclusion) - Body weight - Head circumference	Logistic regression analysis will be performed for SIP, NEC and feeding problems. Linear regression analysis will be performed for body weight and head circumference. Both analyses will be corrected for GA and centre.	Hospital discharge
	**Neurological:** - Intravenous haemorrhage - Clinical seizures - Periventricular leukomalacia	Logistic regression analysis will be performed for all neurological outcomes, corrected for GA and centre.	Hospital discharge

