	**Complications:** - Incidence of late-onset sepsis - Meningitis after inclusion - Need for inotropes/ respiratory support	Logistic regression analysis will be performed for all complications, corrected for GA and centre.	Hospital discharge
	- Retinopathy of prematurity	Logistic regression analysis, corrected for GA and centre, will be performed for retinopathy ‘yes’ or ‘no’.	Hospital discharge
	- Hearing loss	Logistic regression analysis, corrected for GA and centre, will be performed for hearing loss ‘yes’ or ‘no’.	Hospital discharge
**Long-term outcomes**	- Readmission since first hospital discharge - Body weight - Body length - Head circumference - Behavioural problems (Child Behavior Checklist) - Cognitive and language development	Logistic regression analysis will be performed for readmissions, behavioural problems, and cognitive and language problems. Linear regression analysis will be performed for body weight, body length, and head circumference. In both analysis will be corrected for GA and centre. Survival analysis will be performed for the time to readmission.	Eighteen to 24 months of corrected age
**Cost-effectiveness**	- (Non-)medical costs during and after hospital admission - Patient outcomes; survival, severe disability, and health-related quality of life (HRQoL)	The total costs per patient and quality-adjusted life years (QALYs) will be assessed. Incremental cost-effectiveness ratios (ICERs) will be calculated, expressed as incremental costs per additional survivor without severe disability at 2 years and incremental costs per QALY gained.	Eighteen to 24 months of corrected age
**Pharmacokinetics**	- Blood samples	Exposure of (keto-) doxapram will be calculated from an existing PK model. The cumulative exposures will be calculated and analysed using a linear regression model, corrected for centre.	During level 3 NICU admission
**Respiratory effects**	- Vital sign data (oxygen saturation, respiratory rate, heart rate, blood pressure) - Ventilation data (ventilation mode, fraction of inspired oxygen, flow)	Vital sign data will be analysed as continuous data. Logistic regression analysis will be performed for all vital sign data, corrected for GA en centre. Mixed model analysis will be performed to take into account repeated measurements. Ventilation duration and cumulative inspired oxygen need and flow will compared using the *t*-test or Mann-Whitney test.	During level 3 NICU admission

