**Cerebral effects**	- Cerebral oxygenation (rScO_2_; NIRS-derived) - Transfer function (rScO_2_ as surrogate for cerebral blood flow) - Neurological function (General movement assessment) - Cerebral activity (aEEG or full EEG)	Continuous outcome data will be compared using a two-sided stratified MWU (van Elteren test). For dichotomous data, a stratified *χ*^2^-test will be used. A linear mixed model for longitudinal measures using restricted cubic splines to model the relation between time and outcome will be used.	During level 3 NICU admission

Secondary, continuous outcomes will also be presented as mean and standard deviation if normally distributed, and as medians and interquartile range if not normally distributed. The Kolmogorov-Smirnov test will be performed to assess normality of continuous variables. Secondary, categorical outcomes will be presented as frequency and percentage. The outcomes will be compared between the doxapram and placebo group using the *t*-test or the Mann-Withney test in case of continuous data, and the chi-square test or Fisher’s exact test in case of categorical data

^a^The effect measures of logistic regression models will be presented as the odds ratios together with the 95% confidence intervals based on the profile likelihood. For linear regression models, robust standard errors computed with a sandwich estimator will be used for confidence intervals and significance tests. Effect measures of the Cox proportional hazards model will be presented as (conditional) hazard ratios together with 95% confidence intervals. Significance will be tested using the partial likelihood ratio test

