#### Randomization and blinding

Participants will be randomly allocated in a 1:1 ratio, stratified according to study centre and gestational age (<26 weeks or ≥26 weeks), and using random permutated blocks. Multiple birth infants will be randomized independently, unless parents or legal representatives explicitly request that siblings are to be allocated to the same treatment arm. Randomization and drug supply management is performed via an electronic online platform (ALEA®, FormsVision BV, Abcoude, the Netherlands).

Once the participant has been randomized, a study medication kit will be allocated. All treatment kits will be visually identical and contain either doxapram or placebo. The clinical trial centre and trial pharmacy of the Erasmus Medical Centre will manage the randomization list. The parents, researchers and medical team will have no access to the randomization list. Unblinding is only performed by an independent safety officer in emergency situations where knowledge of the study drug is considered absolutely necessary for the clinical management of the included patient.

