### Secondary outcome analyses

Logistic and linear regression analyses will be performed for dichotomous and continuous secondary outcomes, respectively. Regression analyses will be adjusted for GA and admitted centre. Survival analyses using Cox proportional hazards regression will be performed to investigate the relations between the outcomes time to intubation, time to discharge, and time to death. Cause-specific risk models will be computed to consider death as competing risk for severe disabilities. This is done by estimating cumulative incidence functions using the Fine and Grey model [39].

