A limitation of this trial is that the potential direct respiratory effect of the study medication cannot be blinded, although the assessor of the primary outcome will be blinded for the allocated treatment arm. Another challenge is the absence of uniform criteria to evaluate when the frequency and duration of apnoea are considered unacceptable and an intervention is needed. Poets et al. developed an interesting apnoea score to assess the severity of apnoea, but this score is not validated yet and is mostly a reflection of current clinical practice [57]. The rate of apnoea and hypoxic events can also fluctuate largely within and between patients, and detection can be difficult [51, 58]. We therefore chose for a more pragmatic design with less strict inclusion criteria. The decisions to start doxapram in routine clinical care, to adjust its dosage, or to stop doxapram therapy are made by the attending physicians. Enrolment of a participant in the study is done according to the existing clinical protocols and can vary between centres and physicians, as does the dosing and duration of study drug therapy. This pragmatic strategy was chosen to make the trial clinically feasible, relevant and to increase generalizability to other centres. Randomization of participants is stratified per centre, and we will adjust for this stratification in the analysis. The respiratory status before starting doxapram will be evaluated in a subset of the participants using continuous monitoring data. With these data, we aim to find more objective parameters and criteria for the indication to start doxapram therapy in future patients.

This trial will provide knowledge to improve the optimal treatment of preterm infants suffering from AOP. We will evaluate the safety and efficacy of doxapram in reducing death and severe disability in the first years of life. If doxapram is safe and effective, the treatment could be implemented in more NICUs worldwide. The placebo design may also provide the opportunity to identify patients who will benefit from doxapram therapy and those who will not. Evaluation of the exposure to doxapram and keto-doxapram will enable us to optimize dosing in future individual patients. An improved, more individualized AOP treatment policy will likely prevent patients from periods of hypoxemia and unnecessary treatment risks. Overall, this randomized, placebo-controlled trial aims to improve long-term patient outcomes.

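### Cumulative oxygen and flow, and one of two analyses of ventilation duration, are planned as unstratified t-tests or Mann-Whitney tests despite randomisation stratified by centre and gestational age (minor)

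*Protocol article*

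**What the plan says.** The section on randomization and blinding sets an equal allocation between the two arms that is "stratified according to study centre and gestational age (<26 weeks or ≥26 weeks), and using random permutated blocks". For secondary outcomes, the section on secondary outcome analyses gives a general rule: "Regression analyses will be adjusted for GA and admitted centre". The Discussion adds: "Randomization of participants is stratified per centre, and we will adjust for this stratification in the analysis".

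Table 1 applies this unevenly:

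- **Respiration row** (measured at hospital discharge): linear regression for the "number of days on invasive ventilation, respiratory support, and supplemental oxygen. In both analyses will be corrected for GA and centre".
- **Respiratory effects row** (measured during level 3 NICU admission): vital signs are corrected for GA and centre, but "Ventilation duration and cumulative inspired oxygen need and flow will compared using the" t-test or Mann-Whitney test.
- **Cerebral effects row**: a van Elteren test for continuous data and a stratified chi-square test for dichotomous data. The row does not name the strata.
- **Note under the table**, after the descriptive summaries: "The outcomes will be compared between the doxapram and placebo group using the" t-test or the Mann-Whitney "test in case of continuous data, and the chi-square test or Fisher’s exact test in case of categorical data". No stratification is named.

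**The concern.** Blocking within strata balances centre and GA between the arms, so their contribution largely drops out of the treatment difference. An unstratified test still counts that contribution as noise. Its standard error is then too large, its true size falls below 5%, and it misses effects that an adjusted analysis would detect.

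Centre could well matter here. The section on study participants and the Discussion both expect centres and physicians to differ in when they judge apnoea to need intervention. Ventilation and oxygen exposure also lie close to the drug's proposed mechanism.

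Two questions of consistency follow. Ventilation time is adjusted in one row and unadjusted in another. And the note under Table 1 adds an unstratified comparison beside the adjusted models without saying which is the reported result.

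**Working it through.** **Plan's own figure.** The protocol gives no power, variance or stratum effect for these measures, so there is nothing to reproduce. Taken from it: 396 infants, 1:1 allocation, significance at p < 0.05 (read as two-sided), stratification by centre and GA.

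**Assumed.** R² is the share of outcome variance explained by centre and GA stratum. It is not in the documents and is varied from 0 to 0.30.

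**Large-sample formulas.** With total variance σ² and N infants, the treatment difference after blocking has variance of about 4σ²(1 − R²)/N, while the t-test estimates 4σ²/N. Hence:

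- True size = 2[1 − Φ(1.96/√(1 − R²))].
- If the effect gives the adjusted test 80% power (1.960 + 0.842 = 2.802), t-test power = Φ(2.802 − 1.96/√(1 − R²)).

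N cancels from both, so the comparison holds for a subset too, although a smaller subset needs a larger effect to reach 80%.

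**Worked values.**

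- R² = 0.10: 1.96/0.949 = 2.066; size 3.9%; power Φ(0.736) = 76.9%.
- R² = 0.20: 1.96/0.894 = 2.191; size 2.8%; power Φ(0.610) = 72.9%.
- R² = 0.30: 1.96/0.837 = 2.343; size 1.9%; power Φ(0.459) = 67.7%.

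**Check by simulation.** 396 infants, an assumed 12 centres by 2 GA strata, assumed blocks of 4, normal outcomes, 2000 replicates per setting. Monte Carlo standard error is about 0.5 points for size (√(0.05 × 0.95/2000)) and 0.9 points for power (√(0.8 × 0.2/2000)).

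| R² | t-test size / power, formula (%) | t-test size / power, simulated (%) | Mann-Whitney power (%) | Adjusted linear model size / power (%) | van Elteren power (%) |
|---|---|---|---|---|---|
| 0 | 5.0 / 80.0 | 4.5 / 79.8 | 79.1 | 4.6 / 79.5 | 76.7 |
| 0.10 | 3.9 / 76.9 | 4.5 / 76.6 | 74.1 | 5.7 / 80.4 | 74.9 |
| 0.20 | 2.8 / 72.9 | 2.7 / 74.7 | 70.9 | 4.7 / 80.5 | 76.3 |
| 0.30 | 1.9 / 67.7 | 2.2 / 67.1 | 64.8 | 4.4 / 80.1 | 75.9 |

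The Mann-Whitney and van Elteren columns depend only on ranks. They therefore also apply to a log-normal measure whose centre, GA and treatment effects act on the log scale.

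**Same loss with the effect held fixed.** A second simulation used an assumed 20 centres, blocks of 4, 1500 runs, and an effect of 2.80 × 2/√396 = 0.28 SD. Power of the t-test against regression on GA and centre was:

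- 80.7% vs 81.3% with centre explaining 5% of variance and GA nothing;
- 80.0% vs 85.1% with centre 5% and GA 10%;
- 84.5% vs 91.3% with centre 15% and GA 15%.

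Seen this way, the t-test keeps about 80% power and forgoes the gain from adjustment. Part of that gain comes from using GA as a continuous variable, not only from the split at 26 weeks.

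**The case against.** The other side has a good deal in its favour:

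- **The main secondary outcomes are adjusted.** Days on invasive ventilation, on respiratory support and with supplemental oxygen all have a GA- and centre-corrected regression, and the general rule for secondary regressions says the same. A reader might infer that the trial gives away power on ventilation and oxygen exposure generally. The Respiration row does not support that.
- **The note under Table 1 reads as an accompaniment.** It is introduced as an additional presentation of summaries, beside a table column that already gives the models. A reader might infer that every secondary outcome has two rival p-values. The text never ranks them explicitly, but the adjusted regression is the natural main analysis, and a formal ranking may sit in an analysis plan that is not shown.
- **The Discussion is not contradicted.** Its sentence on adjusting for centre is met by the primary analysis and the secondary regressions. It does not promise adjustment of every comparison.
- **The test is valid.** It is conservative, with no bias from ignoring the strata and no inflation of false positives.
- **The size is uncertain.** Number of centres, block size and variance shares are all assumed. The monitor data come from only some centres, so the ventilation measures in this row may also come from fewer than 396 infants.

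These arguments limit the point to one sentence of the table and make it minor. They do not remove it: cumulative oxygen and flow have no adjusted analysis anywhere in the article. The differing measurement times might justify two ventilation measures, but not opposite handling of the stratification factors.

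**Conclusion.** The point holds in narrow form. In the Respiratory effects row, three measures are assigned an unstratified test that does not match the stratified randomisation, the vital-sign analysis in the same row or the tests in the next row. Two of them, cumulative oxygen and flow, have no adjusted counterpart. Ventilation duration sits beside an adjusted analysis of days on invasive ventilation, so the article treats it in two ways.

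The cost is lost power: about 3 points (80 − 76.9) at R² = 0.10 and about 12 points (80 − 67.7) at R² = 0.30, with true size falling from 3.9% to 1.9%. At R² = 0 the cost is nil. The direction is certain if centre and GA are prognostic; the amount rests wholly on the assumed R². Severity is minor, because the primary analysis and the adjusted secondary regressions are untouched.

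**What to change.** 1. In the Respiratory effects row, analyse ventilation duration, cumulative inspired oxygen and cumulative flow with the GA- and centre-adjusted linear regression and robust standard errors already specified in Table 1, on a log or rank scale if skewed. The van Elteren test already used in the Cerebral effects row is an alternative, with the strata named as centre and GA group. In the simulation it was somewhat less powerful than the regression (75% to 77% against about 80%), but it lost little as R² rose.
2. Use the same adjusted analysis for ventilation duration in the Respiration and Respiratory effects rows. If the two are meant as different quantities, say how they differ.
3. State that the unstratified comparisons under Table 1 are supportive or descriptive and that the adjusted estimate is the reported result.

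This is a wording change to make before unblinding. It needs no new data or patients, since centre and GA define the randomisation strata and are known for every infant. The one drawback is that a log- or rank-scale effect is harder to read, so medians and interquartile ranges should stay as description.

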### Secondary short-term outcomes

Secondary outcomes include the respiratory condition of the patient (BPD (NIH 2001 definition [6]), number of days on invasive ventilation, incidence of endotracheal intubation), death (before a postmenstrual age of 36 weeks), duration of NICU and hospital admission, use of postnatal corticosteroids, body weight (at 36 weeks and hospital discharge), solitary intestinal perforation or NEC > stage 2 according to Bell, clinical seizures, intravenous haemorrhage, incidence of late-onset sepsis, meningitis, need for inotropes, retinopathy of prematurity, and an abnormal hearing test at term equivalent age.

### Adverse drug reactions

Adverse drug reactions will be monitored and registered during therapy. For severe events, we refer to the paragraph on safety reporting. Adverse drug reactions will include potassium levels, discomfort or irritability, the occurrence of tachycardia, hypertension, prevalence of convulsions and NEC. Both causality and severity will be evaluated for the possible adverse drug reactions. Causality will be assessed according to Kramer’s algorithm, which can be used to differentiate between possible and probable side effects [31]. The severity of all possible and probable adverse events will be assessed according to the INC Neonatal Adverse Events Scale [32].

### Secondary long-term outcomes

Additional long-term outcomes at 18 to 24 months corrected age will be hospital readmissions, weight, length and head circumference and behavioural problems according to the Child Behavior Checklist [33]. The cognitive and language development will be assessed by the parent-reported PARCA-R questionnaire [34].

Moreover, we will carry out an analysis of cost-effectiveness, including an analysis of health-related quality of life (HRQoL). The potential health and economic gains of doxapram could be substantial due to the low price of doxapram (off-patent) and because it is expected to result in both shorter duration of ventilation, a decrease in length of hospital stay, improved life-long neurological development and less long-term medical needs. We will explore the plausibility of this hypothesis by performing a cost-utility analysis alongside the trial.

#### Sample size calculation

The sample size calculation is based on a cohort study that investigated the long-term neurodevelopmental outcome of preterm infants who received doxapram therapy compared to non-treated matched control patients [20]. This paper described that 30% of the doxapram-treated patients had the composite outcome death or neurodevelopmental delay at 2 years corrected age compared to 50.8% in the non-treated control patients. We therefore consider an absolute decrease of 15% in the composite outcome as clinically relevant, and we aim to reduce the outcome from 50 to 35% with a number needed to treat of around 7 patients. With an alpha of 0.05 and a power over 80%, a sample size of 170 patients is needed per treatment arm when we use a continuity correction. Because we expect approximately 10 patients to be part of twins and a loss to follow-up rate (excluding death) of 10% per treatment arm, the sample size is 198 patients per treatment arm, adding up to a total of 396 patients to be included. Next to the formal consent letter, an animation and flyer are designed providing additional study information to optimize consent and to reach the targeted sample size.

#### Interim analysis and stopping rules

After inclusion of 80 (20%), 200 (50%) and 300 (75%) patients, an interim analysis will be performed to protect the safety, validity and credibility of the trial. There will be no stopping rules for futility. Patient inclusion will be stopped, however, if neonatal mortality is at least 10% higher (absolute difference) in either the placebo arm or the doxapram arm, and if this difference is statistically significant. A difference is assumed statistically significant if a two-sided *p*-value is less than 0.05, based on Fisher’s exact test. The confidence interval for the risk difference will be based on the method of Newcombe [35]. These analyses will not be adjusted for covariates. A reduced set of baseline variables, including at least gestational age and sex, and outcomes, including at least death, BPD and the composite outcome death or severe disability (where already available), will also be studied at the time of the interim analysis.

